#### Secondary analysis and sensitivity analysis

In addition to the primary analysis, further analyses will be conducted. First, again using the primary outcome but including 12 time points (six before the intervention and six after the intervention (measured month-wise), time trends before and after the intervention will be compared using interrupted time-series-models [27, 28]. Secondary endpoints will be analyzed using the same strategy as used in the primary analysis with adjustments of the models as necessary.

Furthermore, descriptive statistics of all collected data will be performed. Continuous variables will be described using means, standard deviations, median, minimum, maximum, and first and third quartile, separately for each intervention group and the control groups as well as for the total population. Categorical variables will be reported using absolute and relative frequencies.

As claims-based data are used, no missing values are expected to occur, therefore no imputation procedures need to be carried out.

#### Analysis sets

The primary analysis will be based on the intention-to-treat sample. This means that, in the analysis, patients will be considered in the treatment arm they were assigned to even if, for instance, not all interventions that were planned in this arm were delivered. In sensitivity analyses, the per-protocol set will be analyzed where these patients will be omitted. Patient to be excluded in this set will be defined before the analysis is performed. In a further as-treated-set the omitted patients will be included again but assigned to the treatment arm that describes best the treatment they actually received.

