### Intervention group

The VESPEERA programme comprises recommended practices regarding discharge and care management, which is reinforced by laws (§ 11 Abs. 4 SGB V, § 39 Abs. 1a SGB V, § 112 Abs. 2, Satz 5 SGB V). The planned intervention picks up these regulations for optimal care and offers suggestions for their implementation and enhancement. Patients will not be randomly assigned to a study arm, but receive different intervention components based on the point of study enrolment and the patient’s medical need (see Table 1 – adjusted SPIRIT figure).

**Table 1 Tab1:** Intervention components for all study arms

Interventions		*Study arm 1:*planned admission into a participating hospital	*Study arm 2:*planned admission into a non-participating hospital	*Study arm 3:*unplanned admission into a participating hospital	*Study arm 4:* unplanned admission into a non-participating hospital	*Study arm 5:* control group, not participating in VESPEERA
GP-practice	Interventions in the GP-practice before admission: (A) assessment for admission (B) admission letter and patient brochure	X	X			
Hospital	Interventions in the hospital: (C) telephonic discharge conversation (D) determination of HOSPITAL-Score and patient discharge information	X				
GP-practice	Interventions in the general practice after discharge: (E) assessment for planning of follow-up care (F) telephone monitoring, depending on the risk for rehospitalisation	X	X	X	X	

Assessment for Admission (A): Before a planned hospital admission, the VERAH collects patient information on basic data, admission diagnosis, medical history, existing prescriptions, medication plans and other medical information, social, living and legal situation, communication and care needs.

Admission letter and accompanying patient brochure (B): Based on the assessment for admission, an admission letter which also specifies how and when the practice is available by phone for the hospital staff is created. Patients receive a brochure that informs and prepares for the hospital stay.

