Telephonic discharge conversation between GP-practices and hospital (C): For patients with complex interventions, medications or post-hospital care needs, a structured telephonic discharge conversation supports cross-sectoral exchange of information and clarification of responsibilities between the participating hospital and the responsible GP. In case of need, the AOK can be contacted to support the discharge process for example by providing medical products/ devices etc. in time.

Determination of HOSPITAL Score and patient discharge information (D): The participating hospitals collect data to determine the HOSPITAL Score, a score that indicates the risk for rehospitalisation within 30 days after discharge [14]. The score is communicated to the GP via the discharge letter. At the time of discharge, the patient receives patient discharge information, which summarizes the documents that the patient receives, follow-up care and appointments after discharge as well as different contact persons according to the respective care needs.

Assessment for planning of follow-up care (E): After hospital discharge, the patient has an appointment in the GP-practice (in case of need: home visit) with the VERAH. They conduct an assessment to determine the patients’ need for follow-up treatment and care. The GP receives a summary of the assessment, disclosing the patients’ care needs. Then, follow-up appointments, prescriptions and applications (such as rehabilitation or home care) can be determined and recorded. The patient receives a short summary of the arranged follow-up care plan. Based on the HOSPITAL Score, the GP determines the patients’ enrolment into the follow-up telephone monitoring. Patients with an intermediate or high risk for rehospitalisation, according to the HOSPITAL Score, should be enrolled in the follow-up telephone monitoring. For patients treated in a non-participating hospital, GP-practices have the option to gather data to determine the HOSPITAL Score. All data necessary to determine the score can be extracted from the discharge letter.

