Post discharge telephone monitoring (F): If the HOSPITAL Score indicates an intermediate or high risk for rehospitalisation, the GP-practice coordinates and accompanies follow-up care through a structured telephone monitoring, which is limited to a time frame of 3 months after hospital discharge. The GP individually defines the content and frequency of the telephone monitoring, which is executed by the VERAH. The first phone call should be scheduled within the first 2 weeks after discharge. The last phone call should be scheduled 3 months after discharge. Any phone calls in between are defined in their interval by the GP.

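### The per-protocol set depends on delivery that a rehospitalisation can itself prevent, in the intervention arms only, so this sensitivity analysis tends to favour the programme

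*Protocol article*

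**What the plan says.** Under Analysis sets, the protocol article makes the intention-to-treat set primary: "The primary analysis will be based on the intention-to-treat sample". Patients stay in their arm even where "not all interventions that were planned in this arm were delivered". For the sensitivity analyses it then states that "the per-protocol set will be analyzed where these patients will be omitted". The only further detail is this: "Patient to be excluded in this set will be defined before the analysis is performed". A third, as-treated set brings the omitted patients back and places them in the arm that best fits what they received.

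Table 1 (Intervention group) marks one row for all four intervention arms and leaves it blank for the control group: "Interventions in the general practice after discharge: (E) assessment for planning of follow-up care (F) telephone monitoring, depending on the risk for rehospitalisation". For E the text says "After hospital discharge, the patient has an appointment in the GP-practice (in case of need: home visit) with the VERAH" and names no day. For F the first call falls within 2 weeks, and "The last phone call should be scheduled 3 months after discharge". The Outcomes section sets the primary window at 90 days. The Control group section says that controls receive none of the components.

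**The concern.** Selecting patients on completed delivery is safe only if delivery is settled before the outcome can occur. Here the two run over the same period. A patient readmitted before the assessment, or while calls are still due, may miss a component because of the readmission, and the rule then drops that patient together with the event. A control with the same course stays in.

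A per-protocol result is usually read as a check on the primary result. If it shows a reduction that comes partly from this selection, it may be taken as confirmation. The Discussion says the results are meant to inform area-wide implementation, so false reassurance would matter.

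**Working it through.** The plan gives no figure for this effect, so there is none to reproduce. The check has two parts.

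**1. Is the mechanism in the text?**
- Omission depends on incomplete delivery (Analysis sets).
- E and F follow discharge in arms 1 to 4, and F extends to 3 months (Intervention group).
- The outcome window is 90 days (Outcomes).
- Controls have nothing to complete (Control group).

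All the links are stated. Nothing under Analysis sets credits a patient who was readmitted before a component was due, and no landmark is set.

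**2. How large could it be?**

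Inputs:
- p = 0.23, the control rate in Sample size calculation, applied to both groups (no true effect).
- f = share of rehospitalised intervention cases omitted. The article does not give it, so a range is shown.
- No case without an event is omitted (relaxed below).

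Formula: per-protocol rate = p(1−f)/(1−pf). The odds ratio against control is 1−f.

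| f | Calculation | Rate | Odds ratio |
|---|---|---|---|
| 10% | 0.207/0.977 | 21.2% | 0.90 |
| 20% | 0.184/0.954 | 19.3% | 0.80 |
| 30% | 0.161/0.931 | 17.3% | 0.70 |

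To give f a time scale, assume that readmissions are spread evenly over 90 days and that all those before day 14 are lost:
- All patients affected: f = 14/90 = 15.6%. The rate is 20.1%, which is 2.9 points below 23%, with odds ratio 0.84.
- Only the 60% expected to be due monitoring (Sample size calculation): f = 0.6 × 14/90 = 9.3%. The rate is 21.3%, which is 1.7 points below, with odds ratio 0.91.

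Extreme case: every readmission among the monitored 60% prevents completion of F. Then f = 60% and the rate is 0.092/0.862 = 10.7%.

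As a yardstick only, the f that would imitate a planned rate t is (p−t)/(p(1−t)). For 15% (arms 1 and 2) it is 0.08/(0.23 × 0.85) = 41%. For 16% (arm 3) it is 36%, and for 17% (arm 4) it is 31%.

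**Relaxing the last input.** If a share g of cases without an event is also omitted, the odds ratio becomes (1−f)/(1−g). Non-delivery unrelated to readmission adds equally to f and g and cancels. The artefact favours the programme when f exceeds g, which is what readmission-driven omission produces. Omitting patients who die without a same-indication readmission raises g and works the other way.

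**The case against.** The strongest reply is that the exact exclusion list is analysis-plan content, and the article says it will be set before the analysis. That is fair for the detail. But the article already states the principle, which is omission for incomplete delivery. Fixing a list in advance does not help if the criterion depends on what happens after discharge.

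Other objections stand and limit the size:
- **Not every early readmission is lost.** E has no stated day and may come first. A monitored patient who is readmitted and discharged again can still receive the month-3 call. A reader might take 10.7%, below the planned 15%, as the likely bias. The text does not support that, because it does not say that calls stop at readmission.
- **Arms 3 and 4 are enrolled after discharge through the practice (Recruitment).** Few patients there could miss E through early readmission and still be in the study. These arms are 3266 + 4899 = 8165 of 1905 + 1905 + 3266 + 4899 = 11,975 expected cases, or 68%. Early loss of E therefore concerns mainly arms 1 and 2.
- **Death is not an outcome event.** It would be wrong to say that every omission favours the programme.
- **The model is difference-in-difference with random intercepts.** The figures above compare simple rates after the start of the intervention. If omitted patients also leave the earlier period, part of the selection may cancel. The article does not say whether they do.

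The as-treated set does return the omitted patients. It assigns them by treatment received, though, and that can itself have been cut short by the readmission. It can share the problem.

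**Conclusion.** The point holds for the per-protocol sensitivity analysis. As stated, the rule selects partly on the outcome, and only among intervention patients, so it tends to favour the programme when there is no effect. The as-treated set can be affected in the same way.

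A reader might infer that the primary result is biased too. It is not biased by this rule, because the intention-to-treat set keeps these patients.

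The size cannot be fixed from the article. Losing 10% to 20% of rehospitalised cases would turn 23% into 21.2% to 19.3%. The day-14 scenarios (21.3% and 20.1%) rest on evenly spread readmissions, on loss of every affected case before that day, and on no omission of event-free cases. They are upper values for their scenarios, not estimates. The change should be made, but it does not threaten the main conclusion.

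**What to change.** Reword Analysis sets in one of two ways.

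1. Judge per-protocol delivery only on components due before the first rehospitalisation or death. No patient is then omitted for a component missed because of that event.
2. Use one fixed post-discharge landmark: define delivery up to it, exclude cases with an event before it in both the intervention and control groups, and count outcomes only after it.

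State the same principle for the as-treated set: reassignment should not rest on components missed because of a readmission or death.

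The cost is wording, with no new data collection. Under option 1, patients readmitted early have fewer components to fail. If non-delivery is common for other reasons, g can then exceed f and the comparison can lean slightly against the programme. It also needs an analysis convention for when E counts as due. Option 2 judges both groups over the same period, but events before the landmark are not counted in this sensitivity analysis. Neither option alters the intervention or the call schedule.

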### Sample size calculation

Since large-scale implementation of the VESPEERA program in a geographical region was intended, the number of participating GPs and hospitals was not restricted. Based on the number of GP-practices who participate in HzV-Care and the number of GP-practices who participate in the PraCMan programme, a number of 115 GP-practices are expected to participate. An estimation of the patient sample size was made using claims-data and several assumptions for hospitalisation rates, rates for planned and unplanned admissions, rates of patients with a high risk of rehospitalisation as well as drop-out rates. Assumptions were made based on analyses of AOK claims-data. Admissions are expected to be planned and unplanned in 50% of the cases, respectively. 56% of planned admissions are made by a GP and therefore can be included in the VESPEERA programme. 40% of planned admissions are cases that are expected to be treated in a participating hospital department. After discharge, we calculated with a 20% drop-out rate for patients who are transferred into a nursing home, who pass away or who do not seek GP contact after discharge. 60% of discharged patients are expected to have a risk of rehospitalisation (HOSPITAL Score indicating an intermediate or high risk for rehospitalisation). Figure 2 gives an overview on the sample sizes in each study arm. Given the estimated sample size, we can estimate the effect size (based on the hospitalisation rates after the intervention) that can be detected. Based on claims-data different numbers of hospitalisations can be expected for each of the intervention groups. The alpha level is set to 5%. The following power considerations are based on chi square tests (to test for group differences) and adjusted for the hierarchical structure of the data. The implemented models in the primary analysis will most likely lead to even higher power values. However, we consider the hierarchical structure of the data with cases nested in patients nested in hospitals or practices, respectively. A relatively high ICC (0.3) can be expected when considering measurements within patients, however the number of cases per patient will be relatively small (approx. 1.6 cases per patient). The clustering by hospitals or practices is taken into account with an expected number of approx. 540 patients per hospital and a presumed ICC of 0.03, which is a realistic value in health services research [20]. Furthermore, we assume a rate of re-hospitalisations of 23% in the control group. With a power of 80%, the following reductions in each of the intervention groups can be shown: For study arm 1 a sample size of 1905 cases can be expected. Hereby, a reduction of approx. 8% (from 23% to approx. 15%) can be shown. The control group will be matched and, therefore, the sample size will be the same. For study arm 2 when compared to the control group, the same reduction is detectable, as the same number of cases can be expected as in study arm 1. In a last step, both the study arms 3 and 4 are compared to the control group using a level of significance of 2.5%. In study arm 3, we expect a sample size of 3266 and, thus, a reduction of approx. 7% (from 23 to 16%) can be shown. In study arm 4, a sample size of 4899 hospitalizations can be expected which allows to show a reduction of approx. 6% (from 23 to 17%).

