#### Primary analysis

In the primary analysis, a difference-in-difference model is applied [21, 25, 26]. The change of the primary outcome (before vs. after the intervention) of each intervention group will be pairwise compared to the control group. Put in a simple way, the following model will be estimated:$$ {\mathrm{rehospitalisation}}_{\mathrm{t},\mathrm{i}}={\upbeta}_0+{\upbeta}_{\mathrm{T}}\mathrm{x}\ {\mathrm{t}\mathrm{ime}}_{\mathrm{t},\mathrm{i}}+\kern0.37em {\upbeta}_{\mathrm{I}}\mathrm{x}\ {\mathrm{i}\mathrm{ntervention}}_{\mathrm{i}}+\kern0.37em {\upbeta}_{\mathrm{I}\mathrm{x}\mathrm{T}}\mathrm{x}\ {\left(\mathrm{intervention}:\mathrm{time}\right)}_{\mathrm{t},\mathrm{i}}. $$

The index t describes the point in time, i is the index for the considered observation. The following parameters will be estimated:β_0_: interceptβ_T_: effect of time; the general change from before to after the interventionβ_I_: difference between groups at baselineβ_IxT_: difference between the change (before and after comparison) in the control and in the intervention group; the main parameter for the outcome evaluation

The assumptions of this model are sufficiently discussed in the literature. The parameter β_IxT_ is the main parameter to evaluate the effectiveness of the intervention, describing the difference in changes between the two groups over time.

The above model is adjusted for the covariate service level of the hospital and the location (general allocation to districts). Other covariates will be already considered during the matching procedure when generating the control group.

The primary outcome is binary. Thus, logistic regression models will be applied. Furthermore, there is a hierarchical structure underlying the data, with cases nested in patients, and patients nested in practices or hospitals, respectively. This structure is considered in the model by including random intercepts at each level. The combination of random and fixed effects results in a mixed logistic regression model. A compound symmetry correlation structure will be assumed when fitting the models.

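### The as-treated reassignment rule does not fit arms that are defined by admission type and hospital rather than by components received

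*Protocol article*

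**What the plan says.** Under Analysis sets, the primary analysis keeps patients in their own arm even if "not all interventions that were planned in this arm were delivered". The per-protocol set omits such patients. A further as-treated set brings them back, each "assigned to the treatment arm that describes best the treatment they actually received". Advance definition is promised only for who is left out: "Patient to be excluded in this set will be defined before the analysis is performed".

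Under Intervention group, the arms do not arise by allocation: "Patients will not be randomly assigned to a study arm, but receive different intervention components based on the point of study enrolment". Table 1 names arm 1 as "planned admission into a participating hospital" and arm 2 as "planned admission into a non-participating hospital". Arms 3 and 4 are the two corresponding unplanned groups, and arm 5 is the non-participating control.

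Under Primary analysis, each arm has its own model: "The change of the primary outcome (before vs. after the intervention) of each intervention group will be pairwise compared to the control group".

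**The concern.** An as-treated analysis relabels patients by the treatment they received. That works when arm labels denote treatments. Here they denote facts about the admission, and a component package is attached to each. Missing a component does not turn a planned admission into an unplanned one, or an enrolled patient into a patient of a non-participating practice.

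Two things are at stake. First, a relabelled case changes the mix of admissions in the receiving arm, so a difference from the primary result may reflect case mix rather than delivery. Second, component E takes place after discharge, when the 90-day outcome period is already running. A patient readmitted before the practice visit may never receive E. If such patients leave their arm, and above all if they are counted as controls, early readmissions are taken away from the programme and possibly added to the comparator.

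**Working it through.** **Inputs.** Component packages come from Table 1, grouped in three blocks: pre-admission (A/B), hospital (C/D) and post-discharge (E/F). As the table was read:

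- arm 1: A/B, C/D, E/F
- arm 2: A/B, E/F
- arms 3 and 4: E/F only, identical to each other
- arm 5: none

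**Step 1: apply the rule.** For each incomplete pattern, count the blocks by which it differs from each arm's package. The arm with the smallest count is taken as the best description. Weighting the three blocks equally is my assumption.

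| Own arm | Received | Nearest arm(s) | Blocks differing |
|---|---|---|---|
| 1 | A/B, E/F | 2 | 0 |
| 1 | A/B, C/D | 1 (stays) | 1 |
| 1 | C/D, E/F | 1, 3 and 4 tied | 1 |
| 1 | E/F | 3 and 4 tied | 0 |
| 1 | A/B | 2 and 5 tied | 1 |
| 1 | C/D | 5 | 1 |
| 1 | nothing | 5 | 0 |
| 2 | E/F | 3 and 4 tied | 0 |
| 2 | A/B | 2 and 5 tied | 1 |
| 2 | nothing | 5 | 0 |
| 3 or 4 | nothing | 5 | 0 |

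Mixing of admission types runs one way, from planned to unplanned. It is certain for planned cases with E/F alone, and possible for the tied C/D plus E/F pattern. The move from arm 1 to arm 2 stays within planned admissions and mixes hospital type instead.

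**Step 2: does the model absorb the move?** Control group lists the patient-level matching variables: Charlson index, indication group, gender and age. Primary analysis adjusts for hospital service level and district. Admission type is in neither list, so nothing stated adjusts for a planned case entering an unplanned arm.

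**Step 3: how many cases?** No failure rate is given for A/B or C/D. The only quantified loss is in Sample size calculation: "After discharge, we calculated with a 20% drop-out rate". It pools death, nursing-home transfer and no practice contact. Applied to the 1905 cases expected in each of arms 1 and 2:

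- if 1905 is before drop-out: 0.20 × 1905 = 381 per arm
- if 1905 is after drop-out: 1905 / 0.80 − 1905 ≈ 476 per arm

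These are ceilings for planned cases that lose E/F through this route. They assume that every drop-out stays in the analysis and that each had A/B. Of these cases, an arm 1 patient with A/B and C/D stays in arm 1 under the rule. Only those with A/B alone fall between arm 2 and control.

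For planned cases that reach E/F without the earlier blocks, only an illustration is possible. Arms 1 and 2 hold 2 × 1905 = 3810 cases; arms 3 and 4 hold 3266 + 4899 = 8165. If 5% to 20% of planned cases had E/F alone (an assumed range):

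- 5%: 0.05 × 3810 ≈ 191 moved; 190.5 / (8165 + 190.5) = 2.3% of the pooled unplanned arms
- 20%: 0.20 × 3810 = 762 moved; 762 / (8165 + 762) = 8.5%

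**The case against.** The primary analysis is by intention to treat, and no significance level, sample size or stated decision rests on the as-treated set. A detailed reassignment table could sit in an analysis plan that is not shown. Both points stand, and they limit the weight of this comment. They do not remove it: the article states a rule, and that rule conflicts with its own arm definitions.

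Four stronger readings are tempting, and the documents do not support them.

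- A reader might infer that the commonest non-delivery has no arm. No rates for the other components are given for comparison. The rule asks for the best description, not an exact match, and an arm 1 case that lacks only E/F stays in arm 1.
- A reader might infer that a moved case loses its matched control and pre-period. Nothing rules out repeating the matching, and the article does not define the pre-period unit. If it is the patient's own earlier claims, it moves with the patient.
- A reader might infer that enrolled patients will be moved to control. The article never says so, and arm 5 is defined by non-participation. The point is only that the rule as worded does not exclude it, although arm 5 is the sole arm whose package matches a case with nothing delivered.
- A reader might treat every missing component as non-delivery. The discharge call (C) is meant for complex cases and telephone monitoring (F) for intermediate or high risk, so their absence can be by design.

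Recruitment also places enrolment of unplanned cases at the practice after discharge. Non-attenders would hardly enter arms 3 and 4, so loss of E/F mainly concerns arms 1 and 2. Finally, the tie between arms 3 and 4 depends on the table as read; a lost cell for arm 3 could break it. Planned cases with E/F alone would still land in an unplanned arm.

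**Conclusion.** The point holds as a misfit between a stated rule and the arm definitions. Following the rule would relabel some planned cases as unplanned, leave others tied between an intervention arm and control, and point to control for cases with nothing delivered. With admission type absent from the listed matching variables and covariates, the as-treated estimate could differ from the primary one for reasons of case mix. Where early readmission is the reason E was missed, reassignment could favour the programme; this direction is reasoned, not calculated.

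The size cannot be fixed from the article. The 381 to 476 per arm and the 2.3% to 8.5% are conditional on the assumptions shown and are not estimates of what will happen. The consequence is confined to a sensitivity analysis: the primary result is untouched, but this analysis could not be relied on to support or question it.

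**What to change.** Reword the as-treated paragraph under Analysis sets so that no case is reassigned across admission type and no enrolled patient is moved to arm 5. Keep each case in the arm set by its admission type and hospital. Examine treatment received as an exploratory analysis within each arm, using components recorded in data already collected: A/B and E/F from CareCockpit, and D from the HOSPITAL Score data. Include C only if its delivery is recorded, since Data sources lists no hospital record of the discharge call. Count E as received only from the date of the practice visit, so that earlier readmissions are not attributed to its absence. Absence of C or F where the programme does not call for them should not count as non-delivery.

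The cost is a change of wording and no new data, provided C is left out where unrecorded. The downside is that the analysis of treatment received stays exploratory.
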